**Treatment strategy during the study:**

The patients will be randomized in the ratio of 3:1 to receive either Amphomul^®^ 15 mg/kg administered as a single dose infusion over 4 to 6 hours or AmBisome 15 mg/kg as a single dose infusion over 4 to 6 hours will be administered on Day 1.

**All the patients recruited will be hospitalized up to Day 7 counting from Day 1 of therapy irrespective of the regimen used.**

# STUDY CALENDAR

Patients **recruited will be hospitalized till Day 7 counting from Day 1 of therapy irrespective of the regimen used.** The evaluation schedules will be as below:

|  | **Screening** |  | | | | **End of Study Visit (EOS)** |
| --- | --- | --- | --- | --- | --- | --- |
| **Visit** | **V0** | **V1** | | **V2** | | **V3** |
| **Days** | **D–7 to**  **D0** | **D1** | **D7** | **D30**  **(+/-5 days)** | **D45***  **(+/- 5 days** | **6 months after study drug administration (‑2 weeks to +4 weeks)** |
| Informed consent | X |  |  |  |  |  |
| Demography and Medical History | X |  |  |  |  |  |
| Systemic Examination | X | X | X | X | X | X |
| Vital signs | X | X | X | X | X | X |
| Eligibility criteria | X | X |  |  |  |  |
| rK39 dipstick test | X |  |  |  |  |  |
| Prothrombin time^##^ | X |  |  | X | X | X |
| Splenic aspirate | X |  |  | X | X | X^###^ |
| HIV test | X |  |  |  |  |  |
| HCV | X |  |  |  |  |  |
| HBsAg | X |  |  |  |  |  |
| Fasting Blood Sugar test | X |  |  |  |  |  |
| Parascreen antigen test | X |  |  |  |  |  |
| Safety  Laboratories | X |  | X | X |  | X |
| X-ray Chest | X |  |  |  |  |  |
| 12-lead ECG | X |  |  |  |  |  |
| UPT(for females of child bearing potential) | X |  |  |  |  |  |
| Treatment Administration |  | X |  |  |  |  |
| DLT Assessment |  | X | X |  |  |  |
| Previous and Concomitant medication | X | X | X | X | X | X |
| Hospitalization |  | X | X |  |  |  |
| Adverse Events | X | X | X | X | X | X |
| *****Visit on Day 45 will be done only for those patients who do not have complete parasitological clearance on Day 30.  ^##^ Prothrombin time will have to be carried out before splenic aspiration and procedure will be done only if prothrombin time ≤4 seconds above the control.  ^###^Splenic aspiration at 6 months will be done only for those patients in whom relapse is suspected. | | | | | | |

# 15. STUDY FORMULATION

## Product information

### 15.1.1 Investigational product (Amphomul^®^)

Amphomul^®^ will be manufactured under Good Manufacturing Practice (GMP) by Bharat Serums and Vaccines Ltd.

Amphomul^®^ will be supplied as a yellowish emulsion for IV injection in 10 mL vials for single use. Each vial contains active ingredients as shown in Table 2.

**Table 2: Composition of Amphomul^®^ per mL of emulsion:**

| Ingredient Amount | |
| --- | --- |
| *Active Ingredient* | |
| Amphotericin B | 5mg |
| *Other Ingredients:* | |
| Soybean oil | 200 mg |
| Glycerin | 22.5 mg |
| Purified Egg lecithin | 12 mg |
| Sodium Hydroxide | q.s. |
| Water for Injection | q.s. |

### 15.1.2 Reference product (AmBisome)

AmBisome will be supplied as 15 mL glass vial (Each vial contains 50 mg Amphotericin B). One pre-packaged, disposable sterile, 5-micron filter will be supplied with this.

**Table 3: Composition of AmBisome per vial:**

| **Ingredient** | **Amount** |
| --- | --- |
| Amphotericin B | 50 mg |
| Hydrogenated soy phosphatidylcholine | 213 mg |
| Cholesterol | 52 mg |
| Distearoylphosphatidylglycerol | 84 mg |
| Alpha tocopherol | 0.64 mg |
| Sucrose | 900 mg |
| Disodium succinate hexahydrate | 27 mg |

## Supply, storage and accountability of study drug

Study drug will be provided by Bharat Serums and Vaccines Ltd. /SIRO for the requested number of patients from time to time depending upon the number of patients likely to be recruited.

### Drug storage

All vials must be stored in a safe and locked place with no access for unauthorized personnel. They must be stored below +25°C and must not be frozen. Storage temperature should be monitored once a day approximately at similar time everyday in a study-specific temperature log provided by SIRO.

In case of AmBisome: the reconstituted product concentrate may be stored for up to 24 hours at +2° to +8° C (36° -46° F) following reconstitution with sterile water for injection, USP. Injection of AmBisome should commence within 6 hours of dilution with 5% Dextrose Injection.

In the event of disruption of the cold chain or accidental freezing, the drugs should not be administered and the Investigator or designee should contact SIRO immediately to receive further instructions and/or fresh supplies.

### Drug supplies

The investigator will be supplied with enough doses of study drugs to administer them as daily IV infusions to each patient as described in the present protocol. An additional 5% of their respective amounts will be supplied for replacement in case of breakage or inappropriate storage conditions.

Amphomul^®^ will be supplied in 10 mL vials, each containing Amphotericin B 5 mg/mL emulsion.

AmBisome will be supplied in 15 mL glass vial each containing 50 mg of Amphotericin B.

In case the container of study drug is broken or unusable, the Investigator should replace it with a fresh vial. Although the Sponsor need not be notified immediately in these cases, documentation of the use of another vial and reason for using it must be recorded by the Investigator on the drug accountability form.

### Drug accountability

The Investigator must acknowledge receipt of study drug supplies for each shipment received.

A drug accountability log should be maintained by the staff responsible for storage/administration of the study drugs to the patient. This should record which supplies are issued to which patients. All times the figures of supplied, used and remaining drug vials should match. All used vials must be kept until the study monitor performs drug accountability and retrieves them.

The drugs supplied for this study are only intended for use in the patients in this study. They must not be diverted for use elsewhere.

The study monitor should be notified immediately of details of any supplies which are inadvertently damaged. Details of any supplies (which are inadvertently damaged or unaccountable for any reason) should be given on this log, which will be collected by the study monitor at the end of the study. At the end of the study, it must be possible to reconcile delivery records with those of used and unused stocks. Account must be given of any discrepancies.

Both used and unused drug vials should be sent back to SIRO for destruction in accordance with provided instructions.

## Randomization and Blinding

- Since this is an open label study, blinding is not applicable.
- Permuted Block randomization schedule with block of size 4 and ratio of 3:1 in the two groups (Amphomul and AmBisome) will be generated for each center.
- Treatment with IP/Comparator drug will begin only after successful screening (signing informed consent and fulfillment of all eligibility criteria).
- After meeting eligibility criteria, the patient will sequentially be allotted to unique subject ID and treatment as per randomization schedule for that center.
- A separate screening and enrolment log will be maintained.
- Neither the Investigators nor patient/patient’s LAR will be blinded to the treatment regimen.

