## Exclusion Criteria

Patients who meet any of the following criteria at screening or prior to treatment assignment have to be excluded from study entry:

1. Patients with past history of treatment with Amphotericin B or any other drug for Visceral Leishmaniasis within 30 days prior to screening.
2. Patients positive for HIV, HCV and HBsAg infection, immunocompromised patients (through history).
3. A history or evidence of any concurrent disease that may be serious or life threatening, significant hematological, cardiac, hepatic, renal, respiratory, neurological or metabolic disease or any condition which, in the opinion of the investigator, may constitute a safety concern or interfere with the evaluation of the study objectives or may prevent the patient from the completing study therapy or subsequent follow-up may have a significant impact on the outcome of the study.
4. Concurrent diabetes, tuberculosis or bacterial pneumonia (on chest X-ray, ESR at screening, past history) or any other infectious or major psychiatric disease.
5. Patients with concurrent Malaria will not be included in the trial. Parascreen antigen test for detection of malarial parasites will be performed at screening visit. Patients diagnosed with malaria could be rescreened for enrollment in the trial after adequate treatment of Malaria; & if the parascreen antigen test for detection of malarial parasites is found negative then the patient could be enrolled in the trial
6. History of major surgery within 2 weeks prior to screening.
7. BUN and serum creatinine >1.5 times ULN, and serum total bilirubin >1.5 times ULN
8. Proteinuria ≥2+
9. Pregnant or nursing women.
10. History of alcoholism or illicit drug use/ abuse, or any condition associated with poor compliance.
11. Known hypersensitivity to Amphotericin B, inactive ingredients of Amphomul^®^ formulation, inactive ingredients of AmBisome formulation.
12. Patients receiving any of the medications prohibited by the study protocol.
13. Simultaneous participation in another trial or received any IP <30 days prior to enrolment.
14. Any condition which in the investigator’s opinion may prevent the patient from completing the study therapy or follow-up

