**Visit 1-(Day 1 to Day 7)**

**Visit 1 - Day 1 (Start of study drug treatment)**

- The patients will be re-evaluated clinically.
- If all eligibility criteria are satisfied, then the patient will be included in the study to receive treatment with Amphomul^®^ or AmBisome.
- Patients not fulfilling any of the eligibility criteria on this visit would not be included in the study and labeled as screening failures.
- Laboratory investigations will be done at Investigator’s discretion.
- Permuted Block randomization with block of size 4 and ratio of 3:1 in the two groups (Amphomul and AmBisome) will be generated for each center. Patients will be randomized in the ratio of 3:1 to receive either Amphomul^®^ infusion (15 mg/kg as a single dose infusion) over 4 to 6 hours or AmBisome 15 mg/kg as a single dose infusion over 4 to 6 hours.
- Test dose consisting of 1 mg will be administered in 5% dextrose over a period of approximately 15-20 minutes prior to administration of full-dose infusion of Amphomul^®^.
- The IP (Amphomul^®^)*,* diluted (maximum dilution allowed to 1 mg/mL) in 5% dextrose will be administered as an infusion.
- Before administration AmBisome has to be diluted with 12 mL sterile water to yield a preparation containing 4 mg of Amphotericin B/mL. This diluted AmBisome will be further diluted with 5% Dextrose to a concentration not less than 1 mg/mL.
- Test dose consisting of 1 mg will be administered in 5% dextrose over a period of 10 minutes prior to administration of full-dose infusion of AmBisome
- No premedication will be administered prior to the study drug administration.
- However, if patient experiences chills or any infusion related reactions after starting infusion, concomitant medication(s) can be administered at the discretion of the investigator.
- As for use of all Amphotericin B products, facilities for cardiopulmonary resuscitation will be kept readily at hand when administering the drug due to possible occurrence of anaphylactic reactions.
- In case of severe hypersensitivity reactions uncontrolled by the premedications or cardiopulmonary complications of hypersensitivity, the patient would be discontinued from the study and would be treated for the complications till the patient becomes stable.
- The patient will be closely monitored for approximately 6 hours following the completion of infusion for any IRTs.
- Vital signs will be recorded.

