**Primary Efficacy Analysis:**

Non-inferiority will be assessed by looking at the lower end of a two sided 95% confidence interval (CI) of the difference Ptest - Pref (the difference in the proportions of patients achieving definitive cure in Amphomul^®^ (Ptest) and AmBisome (Pref). Non-inferiority will be only accepted if the lower limit of the two-sided 95% CI is greater than the non-inferiority margin of -0.10.

Non-inferiority will be tested for both MITT and PP population.

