## Clinical Supplies and Storage

The Investigator will be provided with adequate quantities of the following material to permit completion of the study:

1. IB
2. Latest version of the study Protocol
3. CRFs
4. ICFs
5. IPs

The Investigator should maintain adequate records of the receipt and disposal of all IP supplied. Any unused medication will be returned to SIRO at the conclusion of the study. The Investigator should ensure that the IP is stored in a limited access area and protected from extremes of light, temperature and humidity.

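### A single block of 4 at 3:1 in each centre, disclosed to the sites of an open-label trial, makes up to 44% of allocations predictable before enrolment

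*Protocol*

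**What the plan says.** Section 15.3 (Randomization and Blinding) calls for a "Permuted Block randomization schedule with block of size 4 and ratio of 3:1 in the two groups (Amphomul and AmBisome"), generated for each centre. Section 13 (Visit 1 - Day 1) repeats it: "Permuted Block randomization with block of size 4 and ratio of 3:1". Neither place gives a second block size or any variation in size.

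The list is used in order. Once eligible, "the patient will sequentially be allotted to unique subject ID and treatment as per randomization schedule for that center". On blinding, Section 15.3 states: "Since this is an open label study, blinding is not applicable". It adds that neither investigators nor patients are blinded.

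The sites hold all the information that prediction needs. Section 22.4 (Clinical Supplies and Storage) lists "Latest version of the study Protocol" among the materials given to the investigator. The drug accountability text in Section 15.2 has site staff log which supplies went to which patient.

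Entry is partly a matter of judgement. Section 11.3 restricts enrolment to patients whom the investigator believes will comply with the protocol. Exclusion 14 in Section 12.4 removes anyone with a condition that, in the investigator's opinion, "may prevent the patient from completing the study therapy" or follow-up, and exclusion 3 also rests on investigator opinion. Screening may run from Day -7 to Day 0, and eligibility is judged again on Day 1.

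**The concern.** Each block of 4 holds three Amphomul assignments and one AmBisome. Once the AmBisome assignment has appeared, every remaining patient in that block must receive Amphomul. After three Amphomul assignments, the fourth patient must receive AmBisome. Anyone who knows the block size and has seen the earlier assignments at the centre can work this out.

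Concealment is meant to ensure that the decision to enrol is made without knowledge of the next arm. Here the decision can be informed by that knowledge in a sizeable share of cases. There is also room to act on it, by deferring a patient within the screening window or by using a judgement-based criterion. If patients were steered in this way, the arms could differ in prognosis from the outset. The primary analysis compares definitive cure against a margin of -0.10 (Section 20.2.2), and no later analysis could fully remove such a difference.

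**Working it through.** **Inputs.** Block size 4 and ratio 3:1 by centre (Sections 13 and 15.3); 4 centres and 500 patients, 375 Amphomul and 125 AmBisome (Sections 8 and 11.2). The protocol states no predictability figure, so there is none to reproduce. Its own counts agree: 400/(1 - 0.20) = 500, 500 × 0.75 = 375 and 500 × 0.25 = 125.

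**Definition.** An allocation is certain when only one treatment is left in the block, given the earlier allocations.

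**Enumeration.** The four blocks are equally likely:

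| AmBisome in position | Certain Amphomul | Certain AmBisome | Total certain |
| --- | --- | --- | --- |
| 1 | 3 | 0 | 3 |
| 2 | 2 | 0 | 2 |
| 3 | 1 | 0 | 1 |
| 4 | 0 | 1 | 1 |
| Sum over 16 slots | 6 | 1 | 7 |

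- Share certain: 7/16 = 43.75%. Over 500 patients, 500 × 7/16 = 218.75, about 219.
- Certain Amphomul: 6/16 = 37.5%. This is half of all Amphomul allocations (0.375/0.75 = 0.5).
- Certain AmBisome: 1/16 = 6.25%, about 31 of 500. This is a quarter of all AmBisome allocations (0.0625/0.25 = 0.25).
- By position in the block, the certain share is 0%, 25%, 50% and 100%.

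**Best guess.** Always guessing Amphomul is right 75% of the time. A guesser who switches to AmBisome after three Amphomul is also right in the fourth slot of the block with AmBisome last: 12/16 + 1/16 = 13/16 = 81.25%. The gain is 6.25 points.

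**Alternatives.** The same enumeration for a known fixed block gives 28.6% certain for size 8 and 21.3% for size 12. For randomly mixed sizes, the site was assumed to know the possible sizes but not their order, and to update its prediction after each allocation. By simulation, about 10% of allocations are certain with sizes 4 and 8, and about 4% with sizes 4, 8 and 12 (equal probabilities, about 125 patients per centre).

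**Scale against the margin (assumption, not in the protocol).** Suppose every certain Amphomul slot were filled with patients whose cure rate was higher by d points, and the AmBisome arm were unaffected. The Amphomul rate would then rise by 0.5 × d: 2.5 points for d = 5 and 5 points for d = 10, against a margin of 10 points. This is a ceiling for each assumed d, because it requires every such slot to be exploited in the same direction.

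**The case against.** The strongest reply is that 44% sounds worse than it is. At 3:1 a site already expects Amphomul three times in four, and knowing the block raises best-guess accuracy by only 6.25 points. AmBisome is certain in just 6.25% of slots, so a patient can seldom be steered into the comparator arm knowingly. This stands as a limit on size. It does not remove the concern, because a patient can still be held back from the 37.5% of slots that are certain to be Amphomul.

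Most entry criteria are objective (parasitology, blood counts, liver and renal tests, serology). Sections 13 and 15.3 place randomisation after eligibility has been established. Section 15.3 requires a screening and enrolment log, and Section 22.5 requires a log of all patients attending the centre for the indication, so selective exclusion would leave some trace. All of this is fair. The stated order of events does not stop prediction, however, because the next arm can be deduced before eligibility is judged. A log records exclusions without preventing them.

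Two stronger readings are not supported. A reader might infer that randomisation no longer protects the comparison. In fact 56.25% of allocations remain uncertain, the first slot of every block is never known, and nothing in the protocol shows that anyone would exploit the rest. A reader might also take the block size to be public. The documents show only that it appears in a protocol written for regulatory and ethics submission and supplied to investigators.

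Allocation by centre may also prompt the thought that the confidence interval in Section 20.2.2 should be stratified by centre. That is a separate minor point, commonly left to a statistical analysis plan, and it has no bearing on predictability.

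**Conclusion.** The concern holds as a weakness in the allocation scheme. A fixed block of 4 at 3:1 within each centre, disclosed to unblinded sites, leaves 43.75% of allocations certain in advance, six in seven of them Amphomul. This weakens the protection of randomisation and creates an avoidable opportunity for selection bias. It is not evidence that bias will occur, and its size and direction cannot be derived from the protocol.

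The figure is exact for complete blocks and assumes that site staff know the block size and follow past allocations at their own centre. The protocol makes both possible. Incomplete final blocks matter little: with 4 centres they involve at most 4 × 3 = 12 patients of 500. The change should be made because the weakness is written into the protocol and is cheap to remove.

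**What to change.** For allocations still to be made, regenerate each centre's list with block sizes chosen at random, for example 4, 8 and 12, all at 3:1. Delete the block size from Sections 13 and 15.3, leaving the statement that randomisation is in permuted blocks by centre at 3:1. Keep the sizes in a restricted document at the contract research organisation. The share of certain allocations falls from 43.75% to about 4%, even if sites learn the possible sizes.

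Concealed release of each assignment after eligibility has been logged, by telephone or sealed sequential envelopes, is a useful support. Alone it would not cure the problem, because prediction needs only the block size and past open-label assignments.

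The cost is a new list and an amendment to two sections. Sample size, ratio, endpoints and visits are unchanged. The drawback is a slightly larger possible departure from 3:1 within a centre. If enrolment stops inside a block of 12, up to 12 × 3/4 = 9 Amphomul patients could have no AmBisome counterpart in that block, against 3 in a block of 4.

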## Code Handling and Breaking

In this study since there will be no blinding, code handling and breaking is not applicable.

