## 11.3 Study Design

The study will be prospective, two‑arm, randomized, open-label, multicenter, Phase III clinical study. Patients will be randomized to receive infusion of Amphomul emulsion (15 mg/kg as a single dose infusion) administered over 4 to 6 hours or AmBisome 15 mg/kg as single dose infusion over 4 to 6 hours

Only patients for whom the Investigator believes the requirements of the protocol will be complied with should be enrolled in the study.

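### The open-label randomization procedure does not conceal the next allocation, and its published fixed block of 4 makes 43.75% of assignments certain in advance

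*Protocol*

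**What the plan says.** Protocol Section 15.3 sets out the scheme, and the Day 1 visit text in Section 13 repeats it: "Permuted Block randomization with block of size 4 and ratio of 3:1 in the two groups (Amphomul and AmBisome) will be generated for each center". On how a patient receives an arm, Section 15.3 says: "After meeting eligibility criteria, the patient will sequentially be allotted to unique subject ID and treatment as per randomization schedule for that center". Treatment is open to everyone at the site: "Neither the Investigators nor patient/patient’s LAR will be blinded to the treatment regimen".

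Section 15.4, on code handling, is one sentence: "In this study since there will be no blinding, code handling and breaking is not applicable".

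The screening text in Section 13 puts the eligibility assessment before randomization. Part of that assessment is judgement. Section 11.3 says: "Only patients for whom the Investigator believes the requirements of the protocol will be complied with should be enrolled in the study". Exclusion criteria 3, 10 and 14 in Section 12.4 turn wholly or partly on the investigator's opinion or on expected compliance. Patients may be screened over a week and are re-evaluated clinically on Day 1. Under Section 15.5 the site writes the patient number on the vial label, so there are no pre-numbered packs that could carry a hidden sequence.

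No section shown names a holder of the schedule, a central or telephone release, or sealed envelopes.

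**The concern.** Blinding protects what happens after assignment. Concealment protects the decision to enter the patient, and in an open-label trial it is the main safeguard against selective enrolment. Section 15.4 sets code handling aside solely because there is no blinding, and Section 15.3 supplies nothing in its place.

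An investigator who knows, or can work out, the next arm can enrol, defer or decline a borderline patient accordingly. The AmBisome arm has a quarter of the patients, so a modest number of poor-prognosis patients moved into it lowers its cure rate noticeably and can make Amphomul look non-inferior. Steering in the other direction would penalise Amphomul. Adjustment for recorded baseline factors, such as parasite grade or haemoglobin, can address measured imbalance but not selection on unrecorded clinical impression.

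The analysis sets offer no backstop. In Section 20.1 even the ITT population requires a dose of study drug, so a patient dropped after the arm is known but before dosing is outside it, and non-inferiority is tested on MITT and PP.

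**Working it through.** **The plan's own figures.** Section 11.2 gives 400 evaluable patients (300 + 100), a margin of -0.10, a true difference of zero, at least 80% power and 20% loss. Inflation: 400/(1 - 0.20) = 500, that is 300/0.80 = 375 and 100/0.80 = 125. This reproduces. No cure rate is stated. Solving n(AmBisome) = (1.960 + 0.842)² × p(1 - p) × (1 + 1/3) / 0.10² = 100 gives p(1 - p) = 0.0956, so p is about 0.893. Concealment does not enter this calculation.

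**Predictability with the list hidden.** Inputs are the block of 4, the 3:1 ratio, one schedule per centre and open treatment, all from Section 15.3. Each block holds one AmBisome assignment, equally likely in positions 1 to 4. Once it has appeared, the rest of the block is certain to be Amphomul. If the first three are Amphomul, the fourth is certain to be AmBisome.

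| AmBisome position | Assignments certain in advance |
|---|---|
| 1 | 3 |
| 2 | 2 |
| 3 | 1 |
| 4 | 1 |

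The mean is (3 + 2 + 1 + 1)/4 = 1.75 of 4, or 43.75%. Over 500 patients in complete blocks that is 0.4375 × 500, about 219. By arm, 6 of 12 Amphomul assignments (50%) and 1 of 4 AmBisome assignments (25%) are certain. By the same count, a fixed block of 8 (6:2) gives 28.6% and a fixed block of 12 (9:3) gives 21.3%. If the list is visible, the figure is 100% for any block size.

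**Illustration of the effect (assumptions, not document figures).** Let a share q of patients have poor prognosis, with cure lower by a gap g. Let a share s of those facing an Amphomul slot be deferred to an AmBisome slot, with arm totals kept at 375 and 125.

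- Poor-prognosis share, Amphomul: 375q(1 - s)/375 = q(1 - s).
- Poor-prognosis share, AmBisome: (125q + 375qs)/125 = q(1 + 3s).
- Shift in the cure difference towards Amphomul: g × 4qs.

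The chance of declaring non-inferiority at a true difference of -10 points was found by exact binomial enumeration with 300 and 100 patients and a Wald interval. The ranges cover AmBisome cure rates of 0.80 to 0.95, because the protocol states none.

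| q | g | s | Share Amphomul / AmBisome | Shift | False non-inferiority |
|---|---|---|---|---|---|
| any | any | 0 | equal | 0 | 1.6-2.0% |
| 10% | 10 points | 10% | 9% / 13% | +0.4 points | 2.2-2.4% |
| 10% | 10 points | 25% | 7.5% / 17.5% | +1.0 points | 3.2-3.5% |
| 20% | 20 points | 10% | 18% / 26% | +1.6 points | 4.3-5.3% |
| 20% | 20 points | 25% | 15% / 35% | +4.0 points | 11-19% |

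In the last two rows, 375 × 0.20 = 75 poor-prognosis patients face an Amphomul slot, so deferral of 10% or 25% means about 8 or 19 patients. The nominal one-sided level is 2.5%.

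**The case against.** Several points on the other side carry weight.

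- **Section 15.4 most naturally concerns unblinding codes.** An open-label trial has none to break, and the section does not mention schedule custody. A reader might infer that it waives allocation concealment. Its words do not go that far. What stands is that it gives the absence of blinding as its only reason and that no other section fills the gap.
- **The protocol does not say that sites hold or see the list.** A reader might infer that the whole sequence is open to investigators. A schedule generated for each centre means stratification by centre, not custody there. Section 11.1 places the trial under the CRO's procedures, which are not shown and could cover release. Full foreknowledge is therefore possible but not established. The 43.75% does not depend on it.
- **There are safeguards.** Eligibility comes before randomization (Sections 13 and 15.3). Section 15.3 requires a screening and enrolment log, Section 22.5 a log of all patients presenting with the disease, and Section 22.7 monitoring of the entry criteria. These deter selective entry and leave some trace of it. They do not stop the next arm being known while discretionary criteria are applied.
- **The illustration is assumption-driven.** Nothing in the documents supports a given steering rate, prognosis gap or direction. In the mild cases the error stays close to 2.5%.

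Allocation release is trial conduct at the site, so it is not something that a protocol would ordinarily leave to the statistical analysis plan.

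**Conclusion.** The point holds as a weakness in how the protocol fixes randomization, not as proof of bias. What follows from the document alone is that 43.75% of assignments (about 219 of 500) are certain in advance to anyone who tracks a centre's open allocations, and that no shown provision withholds the next one until entry is irrevocable. With discretionary entry criteria, this leaves the definitive-cure comparison open to selection that the eligibility-first order and the logs reduce but do not prevent.

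The size and direction of any bias cannot be derived. As an illustration only, at a true difference of -10 points and AmBisome cure rates of 0.80 to 0.95, false non-inferiority is about 2.2-3.5% under mild steering and 11-19% under strong steering, against 1.6-2.0% with none. The strong case needs a 20-point prognosis gap and deferral of a quarter of the poor-prognosis patients facing Amphomul. It should not be read as an expected result.

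**What to change.** In Section 15.3, and in the matching Day 1 text of Section 13:

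1. State that the CRO holds the schedule away from the centres.
2. Require the site first to register the patient as consented and eligible in the enrolment log. Only then is the single next allocation released by telephone or fax, or a sequentially numbered opaque sealed envelope opened, with the time recorded.
3. Remove the block size from the site-facing protocol and use randomly varying block sizes that keep 3:1, for example 4 (3 + 1) and 8 (6 + 2).

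Steps 1 and 2 alone would leave the 43.75% untouched, and step 3 alone would not help if the list were visible, so both parts are needed. Varying blocks reduce predictability but do not abolish it.

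In Section 15.4, limit the statement to emergency unblinding so that it cannot be read as covering allocation.

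The cost is a few sentences, a short delay on Day 1 and slight administrative work. The sample size stays at 400 evaluable and 500 enrolled.
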